**Fig. 1 Fig1:**
[figure not shown]
Participant timeline throughout the course of the study

### Data management, collection, and quality control

All surveys for neurologists, MTAs and patients will be conducted electronically via a tablet. The answers will be documented in REDCap, constituting the ALVEEG study database.

REDCap will be programmed using automatic plausibility checks and mandatory fields for data entry. Measures to inquire about missing data by the study personnel will be instituted.

Regular data consistency and plausibility checks will take place in cooperation with the evaluation team, which consequently will contribute to a better quality of documentation in the epilepsy centers. Technical training of the epilepsy centers and study personnel regarding the use of ALVEEG and its AI-supported diagnosis, as well as the documentation in REDCap, will take place prior to the start of the intervention. All questionnaires that were developed specifically for this study were piloted before the start of the intervention.

A data protection concept for the study has been accepted by the data protection officers in charge at the Charité – Universitätsmedizin Berlin. It comprises guidelines with respect to collecting data, data management, transfer, processing, and storage. Data originating from clinical care process and claims data of the participating health insurance companies (primary and secondary data) will be securely transferred from a data integration center (composited of the independent data trust agency (“Treuhandstelle”) at the Charité – Universitätsmedizin Berlin and a team for medical informatics at the Berlin Institute of Health) to the independent evaluating institution at the Charité – Universitätsmedizin Berlin where they will get analyzed and findings will be provided to the studies funding agency.

### Statistical methods: sample size, recruitment and power calculations

The sample size calculation for the presented equivalence trial is based on the primary endpoint. After consultation with the clinical consortium partners, the proportion of resolved clinical cases in the CG is assumed to be 0.8 (80%). We expect to observe an equivalent rate of treatment successes in the IG, whereby (clinical) equivalence is defined within a margin of +/- 15% deviation from the rate in the CG. This corresponds to an equivalence interval of [0.68–0.92] ([68 − 92%]) for the proportion of clinical questions being solved. This margin is based on assumptions made by clinical experts within the consortium and is further supported by the results of international studies on the subject [15].

Based on a significance level of 0.05 and a power of (1-β) = 90%, applying two proportions z-test results in a sample size of 482 participants. Considering an expected dropout rate of about 30%, the sample size of the study amounts to 688 participants. In order to achieve this sample, an average of approximately five patients must be recruited per center and month.

For the secondary endpoints, a power of 0.83 was computed using a two-sided t-test for 550 patients, taking into account the latency period of the routine data from the participating health insurance funds.

According to estimations by the consortium partners and the involved health insurance companies, it is assumed that the aspired sample size can be achieved for all endpoints.

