### Eligibility criteria and patient recruitment

To be eligible to participate in ALVEEG, patients have to (1) have had at least one seizure in the last 12 months or a diagnosis of epilepsy, (2) have an indication 1–4 from OPS 1-210, (3) live in a household with access to at least 4G or faster, (4) be part of the German statutory health insurance system, and (5) present themselves at least at one of the participating epilepsy centers. Patients can only be included if they or their legal representative gave written informed consent. Given the open cohort design of the trial, patients will be continuously recruited by the participating epilepsy centers over the trial duration of 27 months.

Patients are excluded if they (1) have an epilepsy surgery indication (indication 5 from OPS 1-210), (2) present themselves with additional psychosocial needs such as consultation on occupational or driving issues, (3) are privately insured, self-paying patients, or (4) if they or their legal representative does not give informed consent.

In patients with an epilepsy surgery indication, ictal events require some acute neuropsychological testing performed by medical technicians. Therefore, these patients are excluded for medical reasons. Further, patients must have had at least one seizure in the last 12 months or an epilepsy diagnosis to use disease-specific questionnaires during the trial, e.g., the Quality Of Life In Epilepsy (QOLIE-10) questionnaire, to get better insights on seizures relevant for the included population.

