## Discussion

The shortage of inpatient VEM capacities for patients with epilepsy and other seizure disorders in Germany, in addition to the artificial environment of VEMs taking place in hospitals instead of the patient’s usual surroundings, requires better care and access for this population - especially in rural areas, where resources and neurological specialists are limited. As shown in previous studies from other countries, ALVEEGs allow a faster and more effective diagnosis and management of epilepsy and other seizure disorders [7, 8].

We expect that results from this study will deliver insightful evidence on the effectiveness of ALVEEGs in diagnosis and management of epilepsy and other seizure disorders compared to the current inpatient gold standard - not only on the patient and clinical level but also with respect to the German statutory health care system. Further, we will be able to provide a more nuanced understanding of the intervention and its impact, as well as cost-utility and cost-effectiveness results, as we are evaluating different endpoints, while taking into account multiple outcomes and intervention-associated costs.

Nevertheless, there are some limitations to our study. As we collect data from a real-world clinical care setting, we expect missing data to occur, especially when it comes to self-reported information. Being aware of this, we will address this issue through the elaboration of statistical strategies to account for missing values for the different endpoints to be assessed. Further, as blinding of the treating neurologist and data analyst is not possible due to the nature of the trial design, potential bias cannot be ruled out. However, we do not expect any major impact, i.e., bias on the effects to be analyzed.

Finally, claims data from German statutory health insurances are subject to a waiting period for up to 9 months. Therefore, it will not be possible to analyze claims data from all included patients. Further, we will only be able to analyze claims data for patients who are part of the participating three statutory health insurances: BARMER, DAK-Gesundheit and TK. Although in total there are 96 statutory health insurances in Germany, the insurance companies participating in this trial are part of the biggest German statutory health insurances [22]. Hence, we believe that patients for whom claims data will be available are representative of the entire ALVEEG study population.

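### One power figure (0.83 on 550 patients) covers all secondary endpoints, but 550 is too high for the 3-month questionnaires and unsupported for the claims endpoints

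*Protocol article*

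**What the plan says.** All sample size statements are in the protocol article, section on sample size, recruitment and power calculations. For the primary endpoint, "applying two proportions z-test results in a sample size of 482 participants", and then "Considering an expected dropout rate of about 30%, the sample size of the study amounts to 688 participants". For the secondary endpoints, taken together, "a power of 0.83 was computed using a two-sided t-test for 550 patients, taking into account the latency period of the routine data". No effect size, standard deviation or derivation of the 550 is given, and claims latency is the only adjustment named. The section closes by assuming, on the estimates of the partners and insurers, that the target number can be reached for every endpoint.

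Two other sections bear on the 550. Under eligibility, the insurance requirement is only to "be part of the German statutory health insurance system"; membership of a particular fund is not required. In the Discussion, claims data are said to lag by up to 9 months, so that not all included patients can be analysed, and "we will only be able to analyze claims data for patients who are part of the participating three statutory health insurances".

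**The concern.** The secondary outcomes fall into at least three groups with different exposure to missing data:

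- **Questionnaires at the 3-month follow-up** (QOLIE, EQ-5D-5L, its VAS, the PESOS subscale). These depend on patients staying in the study to the last visit.
- **Early study-database measures**, such as waiting time from baseline to electrode placement.
- **Macro-level outcomes**, such as hospital stays, length of stay and inability to work. The article's table of instruments does not list these. The health economic section places hospitalisations in insurer data, so they are read here as claims endpoints.

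One patient number and one power figure cannot describe all three. The number given exceeds what the same section expects to remain after dropout, and nothing shows how it fits with the latency and insurer limits. At stake is how the secondary results are planned and read. A stated power of 0.83 suggests a precision that the 3-month questionnaires will not quite have and that the claims endpoints may miss by a wide margin.

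**Working it through.** **Inputs from the article:** 688 randomised; about 30% dropout; 482 evaluable; control proportion 0.80; equivalence margin 15% of that, so 0.15 × 0.80 = 0.12; secondary power 0.83 at N = 550 with a two-sided t-test; recruitment over 27 months; latency up to 9 months.

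**Assumptions:** 1:1 allocation (not stated, but consistent with block sizes of 2 or 4) and two-sided 5% for the secondary tests (0.05 is stated for the primary endpoint).

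**1. Primary figures.** With two one-sided tests at 5% and 90% power, n per arm = 2 × 0.8 × 0.2 × (1.645 + 1.645)² / 0.12² = 240.5, rounded up to 241, so 482 in total. 482 / 0.70 = 688.6, against the stated 688. Both reproduce.

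**2. What 550 implies.** 550 / 688 = 0.799, a loss of 20%. The plan's own dropout gives 688 × 0.70 = 481.6, or 482. The difference is 550 − 482 = 68 patients, and 68 / 482 = 14%.

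**3. Effect behind the 0.83.** Power comes from the noncentral t distribution with noncentrality d × √(N/4) and N − 2 degrees of freedom. Solving for power 0.83 at N = 550 gives d = 0.249. With d = 0.25 the noncentrality is 0.25 × √137.5 = 2.93 and power is 0.833. The stated figure can only be back-solved in this way, not reproduced independently.

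**4. Latency.** If accrual is uniform and the last 9 of 27 months are lost, 688 × 18/27 = 459 remain, before any dropout or insurer restriction. Conversely, if 550 reflects latency alone, it corresponds to losing 0.20 × 27 = 5.4 months.

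**5. Insurer share.** The article gives none. With no latency loss at all, 550 claims records would need 80% of randomised patients to be in the three funds. If 550 is the number left after latency, essentially all of them would have to be. Shares of 70%, 50% and 30% are assumed for illustration: 550 × 0.70 = 385, 550 × 0.50 = 275, 550 × 0.30 = 165.

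| N | Basis | Power at d = 0.25 | d detectable with power 0.83 |
|---|---|---|---|
| 550 | as stated | 0.83 | 0.25 |
| 482 | 30% dropout | 0.78 | 0.27 |
| 459 | 9-month latency only | 0.76 | 0.27 |
| 385 | 550 × 70% (assumed) | 0.69 | 0.30 |
| 275 | 550 × 50% (assumed) | 0.54 | 0.35 |
| 165 | 550 × 30% (assumed) | 0.36 | 0.46 |

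Starting from 459 instead of 550, shares of 70% and 30% give 321 and 138 patients, with power 0.61 and 0.31.

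**The case against.** The strongest reply is that 482 is not a common ceiling. It was derived for the primary endpoint, and the article does not say when dropout occurs. Waiting time to video EEG is complete once the electrodes are placed, and later dropout cannot remove it. If no more than 20% are lost by then, 688 × 0.80 = 550 remain and the stated power holds. Claims records, too, need not disappear when a patient stops attending. Both arguments stand. A reader might infer that the design delivers 0.83 for no class of secondary endpoint; the article does not support that.

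Second, the sentence ties 550 to routine data, the insurers were consulted on attainability, and the Discussion openly lists both claims limits. A reader might infer that the three-insurer restriction was ignored. That cannot be established, since the 550 is not derived and may already include an expected share. What stands against the plan is that no figure reconciles the 550 with those limits. The Discussion's remarks that the three funds are among the largest, and that their members are representative, concern bias and not patient numbers.

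Third, 459 assumes that the full 9 months of recruitment are lost. Latency is given as an upper limit and no extraction date is stated, so the loss could be smaller. That is fair, and the insurer restriction would still apply.

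Fourth, an effect size for secondary endpoints is often left to the full protocol. Its absence is no fault in a condensed article, but every power value above other than the stated 0.83 rests on a back-solved d.

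Finally, a reader might infer that null secondary results will be taken as proof of no difference. Nothing in the article says so.

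**Conclusion.** The point holds, by class of endpoint.

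- **3-month questionnaires:** the 550 contradicts the plan's own dropout expectation. The size is modest: power about 0.78 instead of 0.83, or a detectable d of 0.27 instead of 0.25.
- **Claims endpoints:** the 550 is unsupported rather than shown to be wrong by a known amount. Full latency alone gives 0.76. The insurer limit takes it lower, and the values from 0.69 down to 0.36 illustrate assumed shares; they do not estimate the true one.
- **Early study-database endpoints:** 550 may be reached, and no error is shown.

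These values rest on d of about 0.25 (back-solved), two-sided 5%, 1:1 allocation and, for 459, uniform accrual with 9 months lost. The mismatch between 550 and 482 needs none of these assumptions. It should be corrected, but it does not threaten the trial: the primary sample size reproduces and is unaffected.

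**What to change.** Replace the single statement with the expected N and the power (or detectable effect) for each class of endpoint, using the effect size that the sponsor actually assumed rather than the back-solved 0.25:

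- (a) 3-month questionnaires at N = 482;
- (b) early study-database endpoints at the number expected at that time point;
- (c) claims endpoints at randomised × expected share insured with the three funds × share past the latency period at data extraction, with both shares stated.

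Qualify the assurance that the sample size is attainable for every endpoint, or label the claims endpoints as estimation only. The cost is a few restated and less favourable figures, plus a request to the three insurers or the centres for an expected membership share. No extra patients and no change to the primary analysis are needed.

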### Sequence generation and randomization procedure

For ALVEEG, a permuted block randomization with block sizes of either 2 or 4 patients [16] was performed at the patient level prior to the start of the trial by an independent data analyst of the evaluation team. Each participating center was assigned its own randomization list.

Given the nature of the trial design, blinding the treating neurologist is impossible. After the patients or their legal representatives have given informed consent and the neurologist has discussed their further treatment strategy with them, patients will be aware of their group allocation.

### Statistical methods

The primary analysis has the aim to evaluate the effect of ALVEEG based on the predefined primary endpoint, the proportion of cases being solved by the video EEG. Two one-sided z-tests will be performed, and a confidence interval will be determined based on the observed difference between IG and CG and interpreted using the predefined equivalence interval, analyzing the proportion of clinical questions being solved in the IG compared to the CG [17]. Point estimates of the intervention effect, together with the corresponding 95% confidence intervals, will be reported on the absolute and relative scale.

For the planned descriptive statistical analyses, mean values (standard deviation) for continuous normally distributed data, medians and interquartile ranges for non-normally distributed continuous data, and the proportions of frequencies for categorical data will be presented.

Depending on the relevant variables, various statistical test procedures and multivariable techniques will be applied in the context of secondary and sensitivity analyses to test the hypotheses within the context of inferential statistics. In principle, the inferential data analyses focus on differences between the IG and CG. For example, to test the difference in duration in days (e.g., waiting time until video EEG or length of in-hospital stay), we will perform a t-test for normal distributions or the Wilcoxson rank sum test for non-normally distributed data.

The entire statistical data analysis will be performed using the statistical software *R* [18] *v4.2.1* (or higher).

Prior to data lock and the actual extraction of the data, a detailed statistical analysis plan, including additional information on ancillary analyses and the handling of missing data, will be developed.

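### The primary z-tests leave the OPS 1-210 indication unused; if it predicts whether a question is solved, some precision may be lost (an efficiency gain, not an error)

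*Protocol article*

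**What the plan says.** In the Protocol article, Statistical methods, the primary analysis is: "Two one-sided z-tests will be performed, and a confidence interval will be determined based on the observed difference between IG and CG". No baseline variable is part of it. The same section places multivariable techniques among the secondary and sensitivity analyses. It announces a later SAP that will add detail on ancillary analyses and missing data.

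Under Eligibility criteria and patient recruitment, every patient must "have an indication 1–4 from OPS 1-210"; indication 5 (epilepsy surgery) is an exclusion. One of four indications is therefore established before anyone is randomised.

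Under Sequence generation and randomization procedure, allocation uses "a permuted block randomization with block sizes of either 2 or 4 patients", and "Each participating center was assigned its own randomization list". Indication is not named as a stratum.

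Under Study outcomes, a question counts as solved by way of a diagnosis, a treatment decision, or both. The numbers of each are also a secondary outcome.

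**The concern.** The trial admits four kinds of indication, and its endpoint covers diagnostic as well as treatment questions. It is plausible, though nowhere stated, that some kinds are solved more often than others. If so, part of the random variation in the crude difference comes from the arms receiving slightly different case mixes. A baseline variable that allocation cannot influence can remove that part, and the plan as stated does not use it.

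The stake is the width of the interval. Equivalence needs both limits cleared, so any narrowing adds directly to the chance of a conclusive result. Timing also matters in a trial where the treating neurologist and the analyst are not blinded: adjustment chosen after an imbalance has been seen is open to challenge, whereas adjustment fixed beforehand is not.

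**Working it through.** **Inputs from the article** (Statistical methods: sample size, recruitment and power calculations): control rate 0.80 with an equal rate expected in the intervention group; margin 15% of 0.80 = 0.12 on the absolute scale; significance level 0.05; power 90%; 482 evaluable, 688 recruited.

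**Assumptions of this check**: 1:1 allocation, one main indication per patient, four equal-sized indications, average rate 0.80. The article gives neither shares nor rates by indication, so the spread is varied from none to large.

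**1. The plan's own figure.** For two one-sided tests at 0.05 each, true difference 0:

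n per arm = 2 × 0.8 × 0.2 × (1.645 + 1.645)² / 0.12² = 240.5, rounded up to 241, so 482 in total. This matches exactly.

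SE = √(2 × 0.16 / 241) = 0.0364. Power = 2Φ(0.12/0.0364 − 1.645) − 1 = 90.1%.

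Dropout: 482 / 0.70 = 688.6, against 688 stated.

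The unadjusted test therefore delivers the power claimed for it.

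**2. What adjustment removes.** Let V be the variance of the solved rate between indications, and R² = V / [0.8 × 0.2]. Adjustment multiplies the variance of the difference by (1 − R²). The SD of the crude difference due to chance imbalance in indication is √(2V/241).

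Worked case, rates 70/77/83/90%: V = (0.10² + 0.03² + 0.03² + 0.10²)/4 = 0.00545, so R² = 0.00545/0.16 = 0.034. Imbalance SD = √(2 × 0.00545/241) = 0.0067, against a total of 0.0364. Adjusted n per arm = 240.5 × (1 − 0.034) = 232.3, rounded up to 233, so 466 in total.

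**3. Range.**

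| Assumed solved rates (%) | R² | Imbalance SD | 90% CI half-width | Power | Evaluable N for 90% power | Patients saved |
|---|---|---|---|---|---|---|
| 80/80/80/80 | 0 | 0 | 0.0599 | 90.1% | 482 | 0 |
| 75/78/82/85 | 0.009 | 0.0035 | 0.0597 | 90.4% | 478 | 4 |
| 70/77/83/90 | 0.034 | 0.0067 | 0.0589 | 91.2% | 466 | 16 |
| 60/75/90/95 | 0.117 | 0.0125 | 0.0563 | 93.7% | 426 | 56 |

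**4. Check by simulation** (40,000 trials per setting, 241 per arm, crude difference against the difference standardised over indication). Under equality both estimators average 0.000. Power, crude against adjusted: 90.2% and 90.3% with no spread, 90.0% and 91.1% for 70–90%, 90.2% and 93.7% for 60–95%. With a true difference of −0.12, equivalence is wrongly declared in 5.0–5.1% of trials by the crude test and 5.1–5.2% by the adjusted one.

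**5. Away from the planning assumptions.** With a true difference of −2 points (0.78 against 0.80), crude SE = √[(0.78 × 0.22 + 0.8 × 0.2)/241] = 0.0371. Power is Φ(0.10/0.0371 − 1.645) + Φ(0.14/0.0371 − 1.645) − 1 = 84%. It becomes 85% with a variance reduction of 3.4% and 88% with 11%.

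**The case against.** The strongest reply is that nothing here is wrong. The crude test is unbiased under randomisation, keeps its 5% error and reaches 90% power at the stated 482. Its standard error already allows for chance imbalance in indication, as for any other baseline variable. All of this stands. A reader might infer that an unlucky case mix would bias the trial, or that it is underpowered; steps 1 and 4 rule out both.

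Second, the article does not describe indications 1 to 4 and gives no case share or solved rate for any of them. Nothing maps the diagnostic and treatment questions of the endpoint onto OPS indication. This stands too. A reader might infer that precision is certainly lost, but the documents support only that it may be, over a range that starts at zero.

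Third, covariate choice can be left to an SAP, and a crude primary analysis with adjusted sensitivity analyses is legitimate. This stands in part. The SAP is the place for the change, but the article does state the primary method and confines modelling to other analyses, so the comment addresses a stated choice and not a missing detail.

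Fourth, the eligibility rule does not say that a single indication is stored as a database field, or that the four exclude one another. That is fair, and the fix has to cover it.

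**Conclusion.** The point holds as an optional improvement in efficiency. The primary analysis leaves unused a baseline item that is fixed before randomisation and not balanced by it. The gain from using it runs from nothing to about 3.6 points of power (56 of 482 evaluable patients) over the assumed spreads, and is about 1 point or less unless the rates differ by more than 20 percentage points. These sizes rest on the assumptions listed above, on one-sided tests at 0.05 (the level that reproduces 482), and on adjustment for indication alone; any gain from centre was not calculated. No conclusion of the trial would be invalid without the change.

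**What to change.** Before data extraction, specify in the SAP:

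- The primary estimate is a risk difference adjusted for the main OPS 1-210 indication recorded at eligibility and for centre, the randomisation stratum. Use Mantel-Haenszel weights, or logistic regression followed by standardisation.
- Both one-sided tests and the confidence interval come from this estimate. It stays on the absolute scale, so the ±0.12 margin carries over.
- A fixed rule pools sparse categories. Four indications by five centres give 20 cells, about 24 evaluable patients each (482/20) if evenly filled and fewer in some if not. A main-effects model is one way to avoid splitting the data so finely.
- A rule assigns one main indication to a patient who meets more than one.
- The crude two one-sided z-tests are kept as a sensitivity analysis.
- The sample size stays at 482 evaluable and 688 recruited.

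The cost is SAP wording, plus a check that the eligibility indication is captured as a field in the study database. If it is, no new data are needed.
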